7.1.2 Information on Research Subjects

At the time of consent acquisition or screening, the following research subject information will be recorded.

1. Date of obtaining consent

2. Subject identification code

3. Background of the research subjects

Age at the time of obtaining consent

Height/ Weight

Prescription drugs

7.1.3 Observations, examination and evaluation items

The test items for each visit are listed below.

**Visit 1** Before bronchoscopy

(This will be done on the same day as the screening, as it is performed as a pre-bronchoscopy examination in routine clinical practice.)

1. Chest CT

Tumor size

Tumor location

Presence or absence of involved bronchi.

Characteristics of tumor

**Visit 2** The day of the bronchoscopy

1. Bronchoscopy

　　　　　The number of bronchial branches can be observed by bronchoscopy

　　　　　Characteristics of large EBUS findings

　　　　　The rate of change to small-diameter GS

　　　　 If the GS is changed to a small-diameter GS, the EBUS findings

Number of biopsies

　　　　　Number of specimens

　　　　　Antibacterial drug for prevention

　　　　　Complications

**Visit 3** When explaining the results of a bronchoscopy

1. Complications

**(**No Visit**)** Pathological examnation

1. Tumor cell count

2.　Sample size

3. Diagnosis of the tissue

4. Evaluability of PD-L1 testing

5.　Proportion of tumor cells in nucleated cells.

**7.2** Provision of samples and information to other organizations

No provision will be made.

**7.3** Handling of Deviations from the Implementation Plan

The principal investigator or research co-investigator will not make any deviations or changes from the study protocol prior to obtaining approval from the head of the institution based on prior review by the Research Ethics Review Committee.

The principal investigators or research contributors may deviate or modify the study protocol for unavoidable reasons such as emergency avoidance, etc., prior to obtaining the prior approval of the research ethics review committee. In such cases, the principal investigators or research contributors will promptly submit the details of and reasons for the deviation or change and the proposed revision of the study protocol or other documents, if necessary, to the Research Ethics Review Committee for approval by the Research Ethics Review Committee and the head of the research institution.

The principal investigator or research co-investigator shall record all deviations from the study protocol, including the reasons for the deviation.

If the principal investigator or research co-investigator learns that the study does not conform to the ethical guidelines for medical research involving human subjects (only when the degree of non-conformity is significant), the principal investigator or research co-investigator must promptly report to the head of the institution, and cooperate with the head of the institution in reporting and disclosing the status and results of the response. After taking the necessary action, the principal investigator or research participant shall cooperate with the head of the research institution in reporting to the Minister of Health, Labor and Welfare or other relevant authorities on the status and results of such action.

# **8****．discontinuance criteria**

If the principal investigator or research co-investigator determines that the study cannot be continued for any of the following reasons, the principal investigator or research co-investigator must stop the study, and document the date and time of discontinuation/withdrawal, the reason for discontinuation/withdrawal, and the course of the study in the medical record and the CRF, as well as performing the necessary tests at the time of discontinuation/withdrawal to evaluate the efficacy and safety.

1. If a research subject declines to participate in the study or withdraws his or her consent

2. If it is found after registration that the eligibility is not satisfied

3. When it is difficult to continue the test due to adverse events

4. If the entire study is cancelled

5. When the principal investigator or research co-investigator determines that it is appropriate to discontinue the study for other reasons.

# **9．Handling of adverse events**

**9.1** Definition of Adverse Events

Adverse events are any unfavorable or unintended signs (including abnormal changes in laboratory values), symptoms, or diseases that occur in conjunction with bronchoscopy, regardless of their causal relationship to the test.

**9.2** Response to Research Subjects in the Event of an Adverse Event

In the event of an adverse event, the principal investigator or research co-investigator participant will immediately take appropriate action and record it without any discrepancy in the medical record and case report form. In the case of discontinuation of the test or treatment for the adverse event, the researcher will inform the subject of the event.

**9.3** Adverse Events to be Reported

All adverse events occurring from the start to the end of the test, whether or not they are causally related to the test, should be reported and observed until the adverse events resolve or are fixed. In addition, all adverse events determined to be causally related to the test should be reported until the end of the study period.

**9.4** Reporting Procedures in the Event of an Adverse Event

All adverse events occurring during the above period will be documented by the principal investigator or research co-investigator without any discrepancies in the medical records and case report forms.

**9.5** Information required for the assessment of adverse events

The severity of an adverse event is defined as: (1) mild: when the patient gets better without treatment by stopping the test alone; (2) moderate: when the test is stopped and some treatment is required, but not severe; and (3) severe: when the test is stopped and the patient needs to be hospitalized or is life-threatening.

・Name of the adverse event

・Name of the adverse event

・Date of conversion

・Outcome: recovery, lightening, with sequelae, no recovery, death, unknown

・Treatment (administration of study drug): no change, discontinuation, withdrawal, reduction, increase in dose, not applicable・Severity: mild, moderate, severe

・Causal relationship with study drug: relevant, not relevant

**9.5.1** Causal relationship between the resilience of adverse events and the study drug

Recovery of an adverse event is defined as the absence of an adverse event or an improvement in status prior to administration. Determination of test causation in adverse events will be based on consideration of the study subject's general condition, comorbidities, concomitant medications/conventional therapies, and time relationship.

**9.6** Handling in the Event of a Serious Adverse Event

**9.6.1** Definition of Serious Adverse Events

Serious adverse events shall be defined as any of the following

1. Death

2. Items that may lead to death

3. Disability (development of dysfunction to the extent that it interferes with daily life)

4. Items that may lead to impairment

5. The patient needs to be hospitalized or extended in the hospital or clinic for treatment.

6. Serious condition according to the cases listed in (1) to (5) above.

**9.6.2** Serious adverse events to be reported

Report all serious adverse events during the study period and any serious adverse events suspected to be related to bronchoscopy after the end of the study (discontinuation).

**9.6.3** Serious Adverse Event Reporting Procedure

When an adverse event occurs and is judged by the principal investigator or others to be serious, the adverse event information will be handled in accordance with the following procedures

1. Report from the principal investigator to the head of the institution and the principal investigator

The principal investigator will report the adverse event information to the head of the host institution and the principal investigator as soon as possible, regardless of the causal relationship. The first report (emergency report) and the second report (detailed report).

2. Report to the Minister of Health, Labour and Welfare

In accordance with the Ethical Guidelines for Medical Research Involving Human Subjects, when the head of an institution determines that a report to the Minister of Health, Labour and Welfare is necessary, the head of the institution shall prepare a "Report of Unexpected Serious Adverse Events" (in accordance with the attached form designated by the Ministry of Health, Labour and Welfare) and report it to the Minister of Health, Labour and Welfare.

3. Handling when additional information is available

when additional information on the event is obtained, the principal investigator of the institution where the adverse event occurred shall submit a report to the head of the institution as soon as possible. The handling of such additional information shall be in accordance with the procedures of (1) and (2).

4. Handlings based on the Drug and Medical Device Safety Information Reporting System

Post-marketing drugs and medical devices will be handled in accordance with the drug and medical device safety information reporting system and reported to the Ministry of Health, Labour and Welfare when necessary.

**10．Discontinuation, suspension or termination of the test.**

# **10.1** Criteria for stopping or suspending the entire study

The Research Office will consult with the principal investigator on the suspension or discontinuation of the entire study when the following information is available and it is considered difficult to continue the entire study

1.Occurrence of unanticipated serious adverse events

2. Information indicating that the trend of occurrence, such as the number, frequency, and conditions of serious adverse events that can be expected cannot be predicted from the package insert.

3.Information on serious adverse events that have been judged to have no causal relationship, but have since been judged to have an undeniable causal relationship based on the number of occurrences, frequency of occurrences, conditions of occurrence and other trends

4. Reports of studies showing that there is a risk of serious disability or death

5. Information suggesting that the study was not validated

**10.2** Information suggesting that the study was not validated

In the event of stopping or suspending the entire study, the principal investigator will promptly notify the head of the research institution in writing, detailing the reason for the stoppage or suspension. They will also promptly inform the research subjects who are receiving the study and take appropriate action, such as changing to appropriate treatment.

**10.3** Procedures for stopping or suspending a study at an individual site

In the event of the suspension or interruption of a study, the principal investigator shall promptly notify the head of the institution in writing and provide a detailed written explanation of the suspension or interruption.

**10.4** Completion of the study

Upon completion of the study, the principal investigator shall notify the head of the institution in writing that the study has been completed and provide a written summary of the study results.

# **11．Study period**

Prospective Case Registry

Ethics Review Committee approval date (July 24, 2018) – December 31, 2020

Retrospective case registration

January 1, 2017 – December 31, 2017

Analysis period: January 1, 2021 – June 30, 2021

**12．Subjects of analysis and statistical analysis methods (main and secondary analyses)**

The following is a summary of the statistical analysis plan for this study.

The statistical analysis plan may revise the summary of this study protocol; however, the study protocol will be revised if the definitions of the primary endpoints and methods of analysis change.

**12.1** Analysis target population

12.1.1 Full analysis set (FAS)

The maximum analytic population (FAS) will be all study subjects who are enrolled in the study, who have undergone bronchoscopy and for whom efficacy data are available. However, subjects in serious violation of the study protocol (e.g., failure to obtain consent, out-of-date enrollment) will be excluded.

12.1.2 Target population (per protocol set (PPS)) in compliance with the study protocol

Study subjects will be eligible for the study, except for cases in which the FAS has found the following serious violations of the study protocol's regulations, including the study methodology

Violation of the inclusion criteria

Violation of the exclusion criteria

All patients will be analyzed after bronchoscopy is completed and the data are fixed. For all efficacy evaluations, analysis in the largest analysis set (FAS) will be the primary analysis, and analysis in the analysis set (PPS) consistent with the study protocol will be performed as a reference.

12.5.1 Tabulation of research subject background

The distribution and summary statistics of the study subject background data in each analytic population will be calculated for each group.

For the nominal variables, the frequency and percentage of categories are shown for each group.

For continuous variables, summary statistics (number of examples, mean, standard deviation, minimum, median, and maximum) are calculated for each group.

When the number of cells with an expected frequency of less than 5 is 20% or more, Fisher's direct probability calculation method is used, and the t-test is used for continuous variables. The significance level is 5% on both sides.

12.5.2 Effectiveness Analysis

12.5.2.1 Main analysis

The number of tumor cells in specimens obtained with large and small GS will be analyzed using a t-test. The significance level is 5% on both sides.

12.5.2.2 Secondary analysis

Analyses of secondary efficacy endpoints will be conducted for the purpose of providing insights that complement the results of the main analysis. The significance level of the hypothesis test is set at 5% for both sides.

12.5.3 Safety Analysis

Investigate the incidence of complications such as hemorrhage and pneumothorax in patients by TBB with large-diameter and small-diameter GS.

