5. Patients who are taking anticoagulants or antiplatelet agents and cannot discontinue them temporarily (except when temporary change to heparin is possible).

6. Pregnant women.

7. Patients judged to be unsuited for this study by their physicians.

**1.4** Number of cases

Expected registrations: 80 prospective registrations

　　　 New enrollment will be terminated when 36 NSCLC cases are obtained by large-diameter GS.

Retrospective registration: 36 cases are assumed; (equal to the number of NSCLC cases obtained with large-diameter GS among the prospective registrants)

Registration Period:

Prospective Registration: Ethics Review Board Approval Date (July 24, 2018) – December 31, 2020

Retrospective registration: January 1, 2017 – December 31, 2017

Analysis period: January 1, 2021 – June 30, 2021

**1.5** Contact information

Name: [name]

Affiliation: Department of Respiratory Medicine, Kobe University Hospital

The address of the research office is [name]

[contact], [contact]

E-mail: [contact]

2．Background and Purpose

**2.1** Background

In Japan, the number of patients with and deaths from lung cancer have been increasing, making it the leading cause of cancer deaths^1)^, and the importance of lung cancer treatment has been increasing. At the same time, new drugs that target genetic mutations such as EGFR and immune checkpoint inhibitors have been introduced one after another, and patients who are eligible for such drugs are experiencing a dramatic increase in survival. Lung cancer practice guidelines recommend selection of therapeutic agents in accordance with genetic mutations in tumor tissue and programmed death ligand 1 (PD-L1) results, increasing the importance of tumor tissue sampling. Pembrolizumab, an immune checkpoint inhibitor, requires tissue confirmation of PD-L1 positivity prior to administration, and more than 100 viable tumor cells are required in tissue for this evaluation^2)^ and sufficient tumor volume is required.

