2.2.2 Secondary purposes

a. Evaluate the rate of lesion delineation for large-diameter and small-diameter GS. (The numerator is the case in which the lesion could be visualized by ultrasound, and the denominator is all cases of large-diameter and small-diameter GS, respectively.)

b. Evaluate the histopathological diagnosis rates of large-diameter and small-diameter GS.(The numerator is the case in which the histological diagnosis was possible, and the denominator is all cases of thick and fine GS, respectively.)

c. Evaluate the number of specimens for which tumor tissue was obtained from all samples obtained from large-diameter and small-diameter GS.

d. Evaluate the size of the specimens of large-diameter and small-diameter GS

e. Evaluate the success rate of PD-L1 testing in large-diameter and small-diameter GS.

f .Evaluate the proportion of tumor cells in nucleated cells in samples of large and small diameter GS.

g. Evaluate the difference in complications such as hemorrhage and pneumothorax between cases with large-diameter and small-diameter GS.

2. Evaluate the rate of change to small-diameter GS, size, location, character, and involved bronchi. Clinical significance: Identifying lesions that are difficult to diagnose with large-diameter GS facilitates the selection of the appropriate type of GS.

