# **5．**Study Method

**5.1** Type and design of the study

　　Prospective intervention trials (historical cohort analysis)

　　　The results of this prospective intervention trial and the result of historical cohort analysis of the small-diameter GS will be performed.

　　Rationale: We used only small-diameter GS until December 2017. In the prospective target group, it is reasonable to use the previous consecutive cases of small-diameter GS use as a historical control.

**5.2** Study outline (see study flow chart)

This is a single-center, historical controlled study to evaluate the benefit of large-diameter GS in patients with peripheral lung lesions.

All 80 study subjects (prospective enrollment group) undergoing TBB for peripheral pulmonary lesions will be performed with a large-diameter GS. When the lesion was invisible in EBUS, we will change to a thinner bronchoscope and TBB was performed with a small GS. Furthermore, we will enroll consecutive patients with NSCLC in whom tissue samples were previously obtained by EBUS-GS TBB using a small GS kit from January 1 to December 31, 2017 (assumed to be 36 cases, retrospective registration group). The primary endpoint of the study will be the difference in the number of tumor cells obtained between the prospective and retrospective groups. The study period will consist of three days: the day before the bronchoscopy, the day of the bronchoscopy, and the day the bronchoscopy results are explained. A summary of the study schedule is shown in Figure 1.

BF

confirm registration

Pathological diagnosis

Primary Registration

consent acquisition

・Group of prospective registration

Screening

test

Pathology specimen evaluation

（count of tumor cells）

・Group of retrospective registration

Pathology specimen evaluation

（count of tumor cells）

・後ろ向き登録群

Registration

**5.3** Case enrollment and allocation methods

The principal investigator or research co-investigator will follow the following procedures from obtaining consent from the research subjects to the start of the study.

1. After obtaining consent from research subjects, the principal investigator or research co-investigator will conduct a screening test to determine the eligibility of research subjects. If the research subject's consent is obtained, the test results before the consent is obtained can be used.

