6.2.2 Safety assessment

complications

　　 Bleeding, pneumothorax, infection and other complications will be evaluated in both groups.

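### Mild complications may be under-counted in the 2017 small-GS controls, which would tilt the descriptive safety comparison against the large GS

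*Protocol*

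**What the plan says.** Secondary purpose g (section 2.2.2) is a between-device contrast: "Evaluate the difference in complications such as hemorrhage and pneumothorax between cases with large-diameter and small-diameter GS". Section 6.2.2 sets the endpoint: "Bleeding, pneumothorax, infection and other complications will be evaluated in both groups". Section 12.5.3 gives the analysis in one sentence: "Investigate the incidence of complications such as hemorrhage and pneumothorax in patients by TBB with large-diameter and small-diameter GS". None of the three sets a severity threshold, or a rule for finding events that applies to both groups.

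For prospective patients, section 7 schedules complications as an observation item on the day of bronchoscopy (Visit 2) and when results are explained (Visit 3). Section 9.1 adds a wide definition: "Adverse events are any unfavorable or unintended signs (including abnormal changes in laboratory values), symptoms, or diseases that occur in conjunction with bronchoscopy", whatever the cause. Section 9.3 opens "All adverse events occurring from the start to the end of the test, whether or not they are causally related to the test, should be", and goes on to require reporting, with follow-up until the events resolve or stabilise. The lowest grade in section 9.5 reads "1) mild: when the patient gets better without treatment by stopping the test alone", so events needing no treatment are in scope.

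The controls are patients whose "tissue samples were previously obtained by EBUS-GS TBB using a small GS kit from January 1 to December 31, 2017" (section 5.2). The revision history dates the first protocol edition 1 May 2018, and section 11 gives ethics approval as 24 July 2018. Section 18.2 explains that controls are not consented individually because some have died or cannot be reached. Section 14.2 lists the source documents: charts, nursing records, laboratory data, images and bronchoscopy reports.

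**The concern.** One group is observed under a protocol that asks for complications at fixed points. The other is read out of records written when nobody was asked to look. A complication that needed action will usually leave a trace either way. Slight bleeding that stopped by itself, or a brief fever, is more likely to be written down in the first group than in the second.

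Because the endpoint is open-ended, such events can enter the comparison. A gap in recording then looks like a gap in safety. If the devices are equally safe, the large GS may appear somewhat worse. If the large GS is truly safer, that advantage may shrink or vanish. Purpose g could not separate a device effect from a recording effect, and no later analysis can restore events that were never written down in 2017.

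**Working it through.** **Figure to reproduce.** The protocol gives no complication rate and no safety power, so there is none on this point. Its one calculated number, 36 per group in section 12.2, concerns the tumour-cell count.

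**Recording in the two groups.**

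| | Prospective group | 2017 controls |
|---|---|---|
| Period | 24 July 2018 to 31 December 2020 | 1 January to 31 December 2017 |
| Scheduled question on complications | Visits 2 and 3 (section 7) | None possible |
| Rule for mild events | Section 9 | None; the protocol did not exist |
| Source | CRF and medical record | Existing records only |
| Common threshold | None stated | None stated |

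The direction follows from the table: under-recording can occur in the controls for events that leave little trace, and it lowers the small-GS incidence.

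**Assumptions for the size** (none is in the protocol):
- Both devices have the same true incidence, made up of major events M and minor events m.
- The prospective group captures all events.
- The 2017 records capture all major events and a fraction c of minor events, with c from 0.50 to 0.75.

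**Formula.** Apparent risk ratio = (M + m) / (M + c × m).

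| M | m | c | Large GS | Small GS | Apparent ratio |
|---|---|---|---|---|---|
| 3% | 7% | 0.75 | 10% | 3 + 0.75 × 7 = 8.25% | 10 / 8.25 = 1.21 |
| 3% | 7% | 0.50 | 10% | 3 + 0.50 × 7 = 6.5% | 10 / 6.5 = 1.54 |
| 3% | 17% | 0.75 | 20% | 3 + 0.75 × 17 = 15.75% | 20 / 15.75 = 1.27 |
| 3% | 17% | 0.50 | 20% | 3 + 0.50 × 17 = 11.5% | 20 / 11.5 = 1.74 |
| 0% | 10% | 0.75 | 10% | 7.5% | 1 / 0.75 = 1.33 |
| 0% | 10% | 0.50 | 10% | 5.0% | 1 / 0.50 = 2.0 |

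With M = 0 the ratio is 1/c at any incidence. That is the upper bound for each c, because any fully captured major event pulls the ratio towards 1.

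**In patients.** With 36 controls and M = 3%, m = 7%, the expected number of control patients with a missed complication is 36 × (10% − 8.25%) = 0.6 to 36 × (10% − 6.5%) = 1.3. The expected shift is about one patient, but against only 36 × 10% = 3.6 expected.

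**Dilution.** Section 12.5.3 compares by device and does not say where prospective patients switched to the small GS are counted. If they make up a share w of the small-GS group and have the same true incidence, the capture of minor events in that group is w + (1 − w) × c. This lies between c and 1, so the bias shrinks but does not disappear while controls remain in the group.

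**After the change.** If the compared events are captured equally in both groups, c = 1 for those events and equal true incidence gives an expected ratio of 1.0. This removes the recording bias only. Other differences between the prospective group and a historical control remain.

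**The case against.** The strongest reply is that the protocol uses two terms, complications and adverse events, and never says that section 9 events feed section 12.5.3. A reader might infer that every section 9 event, laboratory changes included, is counted for the large GS. The text does not support that, because sections 6.2.2 and 12.5.3 do not refer to section 9. This part stands. Even so, complications are asked for at two scheduled visits in one group only, section 6.2.2 ends with an open category, and no stated threshold keeps mild events out.

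Second, the named complications (bleeding, pneumothorax, infection) are likely to appear in 2017 reports, images or charts when they mattered. Section 14.2 lists one set of sources without splitting it by group. This also stands, and it confines the bias to mild events and the residual category.

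Third, section 12.5.3 is descriptive. The 5% tests in section 12.5.2.2 are for secondary efficacy endpoints, and section 15.2 calls the study exploratory. The harm is therefore a biased estimate and not a false test result.

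Fourth, definitions and abstraction rules are often left to the analysis plan or the CRF, and historical controls always carry some limit of this kind. Missing detail alone would not be a finding. But the protocol itself fixes the unequal data collection and the open-ended endpoint. Applied as written, they bias the contrast for mild events, and this can be avoided for events that leave documentation.

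**Conclusion.** The point holds in a limited form. Mild complications may be under-counted in the small-GS controls, and this would tilt the descriptive contrast of purpose g against the large GS. The direction rests on the dates and the recording rules in the protocol. That routine 2017 records hold fewer mild events is a reasonable inference, not a documented fact.

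Under the stated assumptions (3 of 10 percentage points major, 50 to 75% capture of minor events, equal true incidence), the apparent risk ratio is about 1.2 to 1.5. A reader might take 1.33 to 2.0 as the expected distortion of the whole comparison. That range applies only if every complication is minor, so it is an upper bound. A reader might also infer that the large GS will show an excess that is then inflated, but the protocol neither states nor predicts one. Counting switched prospective patients as small GS would dilute the bias further.

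This is a cheap improvement to a secondary safety comparison. It does not touch the primary endpoint.

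**What to change.** In sections 6.2.2 and 12.5.3, limit the between-group comparison to complications that leave documentation in both periods:
- pneumothorax seen on imaging;
- bleeding with a documented intervention;
- infection with documented treatment;
- events that caused or prolonged a hospital stay.

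Abstract these in both groups by one written rule from the same source records named in section 14.2. For the prospective group this means using those records for the comparison, and not the CRF prompts. Report all other adverse events for the prospective group only, without comparison.

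The cost is protocol wording and one abstraction rule applied to records already listed. The downside is that minor events are described for the prospective group but not compared between devices.
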